### Sample size {14}

To estimate the required sample size, Monte Carlo simulations were carried out using Stata 16.1 with the following assumptions: Two measurement points of 15 secondary schools per group with 10 classes per school and 5 primary schools per group with 4 classes per school are expected to take part in the study. In each class, 25 pupils are expected. Baseline bullying prevalence is estimated to be 15%, and the intervention is expected to lead to a relative reduction in bullying of 25%. The standard deviation (*SD*) of bullying rates between schools is *SD* = 0.2 on the logit scale; the *SD* of classes within schools is *SD* = 0.4 on the logit scale. This leads to an intraclass correlation coefficient on the school level of 0.011 and 0.057 on the class level. The assumptions were chosen so that the simulated data corresponded to the data from the OBPP study [18]. With these assumptions, 1000 data sets were simulated and analysed by three-level mixed logistic regression with group, measurement point, and their interaction as fixed effects and random intercepts on the school (level 3) and class (level 2) level. Using an alpha-error probability of 0.05, with 40 schools and 8500 pupils (4250 IG and 4250 CG) the power would be 86%.

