## Statistical methods

### Statistical methods for primary and secondary outcomes {20a}

For the primary outcome (i.e. reduction in victimization and perpetration rates in IG compared to CG; see first objective), three-level mixed effect regressions with the dependent variables bullying victims (yes/no) and perpetrators (yes/no) will be conducted. For secondary outcomes (i.e. reduction in psychological distress, self-harming behaviour, and problematic Internet use in IG compared to CG; see second objective), dependent variables will be scores of the KIDSCREEN-27, SDQ, self-harming behaviour, IGDS, and SMDS (grades 5 to 9) or the scores of the KIDSCREEN-10 (grades 3 and 4). The fixed effects are the factors group (IG, CG), measurement point (T0, T1, T2), and the interaction of both (group × measurement point). The hierarchical random effects are the factors school (level 3) and class (level 2). The analyses are conducted using Wald tests (interaction group × measurement point). In order to investigate the third objective (i.e. effectiveness of specific program components), a variable reflecting the implementation of a specific component of the program (assessed via teacher surveys as well as via eLearning utilization) is included as a covariate and as an interaction term with group, measurement point, and their triple interaction in the model. The triple interaction allows for the identification of the effectiveness of a specific program component. The analysis is repeated for different components. The fourth objective (i.e. individual characteristics predicting program success at the individual level) is investigated by adding a pupil level to the multilevel analysis. The association of surveys from different time points to pupils is ensured by individual codes. Codes with a Levenshtein distance not greater than 2 are assigned to the same pupil. For each individual characteristic (i.e. personality traits, internal self-blame, callous-unemotional traits), the model of objective one is extended by the characteristics at baseline as a predictor and a pupil specific random intercept. In order to compensate for the small number of randomized schools, we will apply a small sample error correction to each analysis using school-level bootstrap. All calculations are performed with a significance level of 0.05.

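### The primary test subtracts the chance baseline difference in full; adjusting for T0 instead would cut the variance of the T1 bullying contrast by about 27–29% under the assumptions that reproduce the stated power

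*Protocol article*

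**What the plan says.** The section on statistical methods for primary and secondary outcomes {20a} sets out a three-level mixed model for victim status and for perpetrator status: "The fixed effects are the factors group (IG, CG), measurement point (T0, T1, T2), and the interaction of both". School and class are the random effects. The test is named directly: "The analyses are conducted using Wald tests (interaction group × measurement point". The secondary outcome scores use the same structure.

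The sample size section {14} powers that contrast with two measurement points. The simulated data were analysed "with group, measurement point, and their interaction as fixed effects and random intercepts on the school (level 3) and class (level 2) level". The result is: "Using an alpha-error probability of 0.05, with 40 schools and 8500 pupils (4250 IG and 4250 CG) the power would be 86" per cent.

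No baseline covariate and no equal-baseline constraint is stated for the primary outcome. The baseline level of victimisation appears only under additional analyses {20b}, as a possible influence on effectiveness. The article gives no T0–T1 correlation and does not say whether class effects carry over from one wave to the next.

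**The concern.** Schools are randomised 1:1, so the expected T0 difference between arms is zero and any observed difference is chance. The free interaction removes that difference with weight 1. This is the best weight only if T0 and T1 correlate almost perfectly. At a lower correlation, the subtraction brings in more T0 noise than it takes out of T1. Weighting T0 by its actual relation with T1 addresses the same treatment question with a smaller standard error.

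The stake is precision. School recruitment ended in September 2023, so the analysis is one of the few remaining ways to gain power. The data needed are already collected.

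**Working it through.** **Inputs (sample size section {14}).** Clusters per arm: "15 secondary schools per group with 10 classes per school and 5 primary schools per group with 4 classes per school", that is 20 schools and 15×10 + 5×4 = 170 classes. "In each class, 25 pupils are expected", so 170×25 = 4250 pupils per arm. "The standard deviation (*SD*) of bullying rates between schools is *SD* = 0.2 on the logit scale" (variance 0.04); the class SD is 0.4 (variance 0.16). "Baseline bullying prevalence is estimated to be 15%, and the intervention is expected to lead to a relative reduction in bullying of 25" per cent, so 15% against 11.25%. Alpha is 0.05, taken as two-sided because sidedness is not stated.

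**Effect on the logit scale.** logit(0.15) − logit(0.1125) = 0.3309.

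**Variance components of one arm at one wave**
- School: 0.04/20 = 0.00200
- Class: 0.16/170 = 0.00094
- Sampling at 15%: 1/(4250×0.1275) = 0.00185
- Sampling at 11.25%: 1/(4250×0.0998) = 0.00236

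**Step 1: reproduce the 86%.** Let school effects persist and class effects be redrawn each wave, with no pupil-level correlation. The school term cancels in the difference-in-differences:
- Variance = 4×0.00094 + 3×0.00185 + 0.00236 = 0.01166 (unrounded terms); SE = 0.1080
- Power = Φ(0.3309/0.1080 − 1.96) = 86.5%

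If class effects also persist, power is 96.1%. If all effects are redrawn, it is 65.5%. Of these three variants, only the first matches the article.

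**Step 2: adjust for T0 under the same assumptions**
- Variance of the T0 arm difference: 2×(0.00200 + 0.00094 + 0.00185) = 0.00957
- Variance of the T1 arm difference: 0.01008
- Covariance (the school part of both arms): 2×0.00200 = 0.00400
- Adjusted variance: 0.01008 − 0.00400²/0.00957 = 0.00841
- Cut: 1 − 0.00841/0.01166 = 28%; power = Φ(0.3309/0.0917 − 1.96) = 95%

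With all cells at 15%, the correlation is r = 0.00400/0.00957 = 0.418 and the cut is (1 − r)/2 = 29%. Generalised least squares with the actual 15×10 + 5×4 structure gives 27%. With 27 secondary and 13 primary schools, the mix described under recruitment {15}, the cut is 28% and power goes from 85% to 94%.

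**Step 3: vary what the article does not give.** These are assumptions.

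| Assumption | Variance cut |
|---|---|
| Class redrawn, no pupil correlation | 27–29% |
| Class redrawn, pupil T0–T1 correlation 0.3–0.5 | 17–21% |
| Class redrawn, school-by-time variance 0.01–0.04 | 30–34% |
| Class effects persist | 18–19% |
| Class effects persist, pupil correlation 0.3–0.5 | 8–12% |

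The range is about 8–34%.

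**Step 4: cost of estimating the slope.** These figures take the T0 weight as known. Estimating one slope from 40 schools in two arms inflates the variance by about 1 + 1/(38 − 2) = 1.028. The 28% cut becomes 1 − 0.722×1.028 = 26%; the 8% cut becomes about 5%.

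All of this concerns the T0–T1 contrast, uses large-sample variances and leaves out the planned school-level bootstrap.

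**The case against.** The strongest reply is that nothing in the plan is wrong. The power section and the analysis section use the same kind of model, the trial is powered for that contrast, and the interaction directly estimates the outcome as defined: change from T0 in one arm against the other. That stands; this is lost efficiency and not an error.

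The size of the gain is also open to challenge. The correlation of 0.42 assumes that a pupil's own answers are unrelated over a year, although many of the same pupils are surveyed again. This stands too, and is why a range is given.

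A reader might infer that the trial forgoes the equivalent of about 40% more schools (1/0.71 = 1.41) in every primary and secondary comparison. The article does not support that: it gives no variance components for KIDSCREEN, SDQ, self-harm, IGDS or SMDS, and for bullying the figure holds only under the Step 1 assumptions.

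A reader might also infer that baseline adjustment can never lose. That is not so for the planned model with the group effect simply removed. Such a model weights T0 by its working correlation b, giving variance v(1 + b² − 2br) against 2v(1 − r), where v is the variance of the arm difference at one wave. It loses when r exceeds (1 + b)/2. With persisting class effects (b = 0.61), the ratio is 0.89, 1.00 and 1.10 at pupil correlations of 0.3, 0.5 and 0.6. The article quotes retest values of 0.62 for the SDQ and 0.61–0.74 for KIDSCREEN-27, so this matters for those outcomes. An estimated coefficient largely avoids the problem: with the 1.028 factor it loses only if r exceeds 2/1.028 − 1, about 0.95.

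Finally, an unaffected T0 cannot be taken as given. The concealment section {16b} says that randomisation came before baseline and that principals and core teams were told the allocation. Core teams are made up of teachers and social workers, and they coordinate the baseline surveys. Pupils choose study participation at each survey. Teachers and pupils in general were not to be told, which limits the risk but does not remove it. A model that forces equal T0 means would be exposed to this; the free interaction is more robust to lasting differences between arms.

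**Conclusion.** The point holds as one of efficiency. The free interaction is a valid test and reaches its stated power, but it uses T0 poorly. Under the assumptions that reproduce the 86%, baseline adjustment cuts the variance of the T1 bullying contrast by 27–29% (about 26% after paying for the estimated slope) and raises power at a 25% reduction from about 86% to about 95%.

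The T0–T1 correlation behind these figures is implied by one reading of the planning assumptions and is not stated in the article. Elsewhere in the range examined the gain is roughly 8–34%, positive in every scenario computed with the correct weight. It cannot be quantified for secondary outcomes. The change is worth making, but the trial does not fail without it.

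**What to change.** **Primary estimate.** Fit the same three-level model to follow-up data and report the group effect at T1, and likewise at T2. Adjust for the school's T0 prevalence with an estimated coefficient and keep the planned school-level bootstrap. For continuous secondary outcomes use the school's T0 mean score.

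**Sensitivity analysis.** Keep the unconstrained group × measurement point interaction. A marked disagreement between the two would point to a T0 difference that adjustment does not handle.

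**If a common-baseline model is preferred.** It must keep both group × T1 and group × T2; with only the first, the arms would be forced equal at T2. It must also allow for correlation within pupils or use robust errors.

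**Avoid as the main adjustment** the pupil's own T0 status: it is available only for consenting pupils whose codes link, and in a logistic model it changes the odds ratio being estimated.

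**State the caveat** that allocation was known to principals and core teams before T0, so T0 could be slightly affected.

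**Cost.** A short change to {20a}, made before the analysts are unblinded. No new data or pupil linkage is needed. A school without a T0 survey would need a stated rule.

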## Interventions

### Explanation for the choice of comparators {6b}

The IG will immediately start with the implementation of *Bullying&You*. Since bullying is known to have a variety of harmful consequences, it would be unethical to prevent schools in the CG from receiving the anti-bullying program. Therefore, we decided to compare the IG with a waiting CG that will implement the program with a delay of 1 year. Furthermore, past research shows that it can be very difficult to recruit schools for a randomized trial design [16]. This is most likely to be successful if schools in the CG are promised to receive the same treatment as the IG but with a specified delay. In order to keep the motivation in the CG comparably high as in the IG and to bridge the waiting time, teachers in CG schools obtain psychoeducational material regarding bullying.

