### Relevant concomitant care permitted or prohibited during the trial {11d}

Already established unsystematic or single anti-bullying efforts (such as a letter box to anonymously report bullying incidents) are permitted, but other whole-school bullying prevention programs than *Bullying&You* are prohibited during the trial.

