#### Third objective

To get insight into the effectiveness of specific components of the program, short surveys for teachers will be conducted at T1 and T2. Furthermore, the use of the eLearning platform is recorded continuously (i.e. the proportion of completed eLearning units).

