In secondary schools, pupils who agree to participate in the accompanying research also fill in:Attributions for Victimization Experiences Measure ( [37, 38]; 17 items): Cronbach’s alpha = 0.71–0.80 for the subscalesInventory of Callous-Unemotional Traits—Youth Version (ICU; [39]; 24 items): Cronbach’s alpha = 0.77

All measures are well tested standard instruments and have previously been used in adolescent samples.

In addition to the pupil survey, the evaluation of the program relies on documentation of the actual program components implemented at each school through an annual teacher survey. For this purpose, teachers receive an invitation to an anonymous online survey (T1: only IG; T2: IG and CG), taking a maximum of 5 min to answer. In the questionnaire, all teachers are asked to estimate the workload and the benefit of the program and get the opportunity to give feedback to the program. Class teachers are additionally asked about the amount of eLearning units, class meetings, and project days in their class. Furthermore, the use of the eLearning platform by pupils and teachers is evaluated (i.e. what is the proportion of completed eLearning lessons).

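### The group × measurement point × component interaction does not identify a component's effectiveness: it is not estimable with a concurrent or T1-based score, and is a non-randomised association under any coding

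*Protocol article*

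**What the plan says.** The protocol article, section Statistical methods for primary and secondary outcomes {20a}, takes the model with group, measurement point (T0, T1, T2) and their interaction and adds a variable for how far a component was implemented. This variable is "assessed via teacher surveys as well as via eLearning utilization" and "is included as a covariate and as an interaction term with group, measurement point, and their triple interaction in the model". The section then states: "The triple interaction allows for the identification of the effectiveness of a specific program component".

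The data behind the variable are described elsewhere:

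- Plans for assessment and collection of outcomes {18a}: teachers receive an "invitation to an anonymous online survey (T1: only IG; T2: IG and CG". No implementation survey is stated for T0.
- Third objective: "the use of the eLearning platform is recorded continuously (i.e. the proportion of completed eLearning units".
- Explanation for the choice of comparators {6b}: the comparison is with a "waiting CG that will implement the program with a delay of 1 year".
- Section {11d}, on concomitant care, allows some existing measures to go on: "Already established unsystematic or single anti-bullying efforts (such as a letter box to anonymously report bullying incidents) are permitted".

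Section {20a} does not say whether the component variable changes over time or is one value per school, nor what value a CG school takes at T1. Section {20c} mentions one intensity score per school, but for dose sub-analyses. The Objectives section calls the third objective exploratory.

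**The concern.** A triple interaction compares two things: how the change in bullying depends on the component in the IG, and how it depends on the component in the CG. Up to T1 the CG has no program and no teacher survey, so with implementation as it stands at T1 there is nothing in the CG to compare with. By T2 the CG has implementation data, but it is also running the program.

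An analyst who follows the text with the obvious coding will therefore meet duplicated columns. Software may drop one without comment. What is left at T1 is an association among IG schools between amount implemented and change in bullying, and the protocol's sentence licenses reporting it as the effectiveness of the component. Schools that implement more may differ in staff, climate and baseline bullying. The Background section hopes that component results will guide policy and later programs, so a confounded estimate could misdirect that work.

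**Working it through.** **The plan's own figure.** None is given for the third objective. The stated 86% power concerns the group × measurement point interaction. It reproduces as follows: ln OR = logit(0.1125) − logit(0.15) = −0.331; variance = 3/(4250 × 0.15 × 0.85) + 1/(4250 × 0.1125 × 0.8875) + 4 × 0.16/170 = 0.0117; SE = 0.108; two-sided power at 0.05 = 86.5%. The last variance term assumes class effects drawn anew at each measurement point. This figure neither supports nor weakens the present point.

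**Counting rule.** With 2 groups and 3 measurement points there are 6 cells. The model with all interactions gives each cell its own intercept and its own component slope b, hence 12 columns. An intercept needs records in the cell. A slope needs a component score that varies in the cell. The rank is the number of intercepts plus the number of slopes that the data supply. The triple terms are:

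- T1: (b_IG,T1 − b_IG,T0) − (b_CG,T1 − b_CG,T0)
- T2: (b_IG,T2 − b_IG,T0) − (b_CG,T2 − b_CG,T0)

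Each needs all four of its slopes.

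**Results by coding.** The ranks were confirmed numerically for 40 schools, 20 per group. In the first two rows the score is 0 in both groups at T0.

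| Component score | Intercepts | Slopes | Rank | Triple terms estimable |
|---|---|---|---|---|
| At each time, CG T1 set to 0 | 6 | 3 (IG-T1, IG-T2, CG-T2) | 9 of 12 | neither |
| At each time, CG T1 missing | 5 | 3 (same) | 8 of 12 | neither |
| Fixed T1 score, CG = 0 | 6 | 3 (IG only) | 9 of 12 | neither |
| Fixed T1 score, CG = 0, T0/T1 only | 4 | 2 (IG only) | 6 of 8 | no |
| Fixed T1 score, CG missing | 3 | 3 (IG only) | 6 of 12 | neither; all 20 CG schools drop out |
| One constant score per school, CG from T2 | 6 | 6 | 12 of 12 | both |

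In the fixed-score rows with CG = 0, the component column equals component × group, and component × T1 equals the T1 triple term. Setting the CG to 0 is itself an assumption. Single measures such as a letter box are allowed in the CG, and no CG survey at T1 would record them.

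**What the full-rank coding estimates.** The T1 term asks whether the IG–CG difference in change varies with the score. In the CG, that score is implementation measured after the T1 outcome. The term is interpretable only if later CG implementation stands in for what those schools would have implemented had they started at once.

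The T2 term does not measure effectiveness. Suppose the baseline slope is s in both groups and the component shifts the T2 slope by β in both. The term is then (s + β − s) − (s + β − s) = 0, whatever the size of β. In general it contrasts the IG in its second program year with the CG in its first.

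**Randomisation.** Schools were randomised to start now or later, not to components. By the protocol's own account, schools without digital equipment may leave out pupil eLearning {11b}, core teams adapt components to their school and two components are optional (Table 1), and primary pupils receive no eLearning {11a}. Pupil eLearning use is thus tied to school type and infrastructure.

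**The case against.** The strongest reply is that the protocol leaves the coding open, that coding is properly a matter for an analysis plan, and that one coding built only on planned data makes the model estimable exactly as written: a constant score per school, with CG values from the T2 survey. Use of the eLearning platform is also logged throughout. This stands. A reader might infer that the model cannot be fitted at all, but the documents do not support that. Even a rank-deficient model runs once aliased columns are dropped, and CG implementation is observed at T2.

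A reader might also infer that the protocol presents a randomised component effect. It does not say so. It calls the objective exploratory, and its Discussion warns that components may work only in combination and that conclusions will need care. Nor does the rank argument carry over to the dose sub-analyses in {20c}, for which no model is given.

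The reply does not rescue the sentence itself. The point is not that a coding is missing but that the article makes a positive claim about what the triple interaction delivers. That claim fails under concurrent and T1-based scores because the terms are not estimable. It fails under the constant score because the T2 term has the wrong meaning and the T1 term needs an unstated assumption. Under every coding it fails because implementation was not randomised.

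**Conclusion.** The statement that the triple interaction identifies a component's effectiveness is wrong as written. With a concurrent score the design is short by 3 columns (CG T1 = 0) or 4 columns (CG T1 missing) out of 12. With a fixed T1 score and CG = 0 it is short by 2 of 8 for T0/T1. Neither triple term is estimable in these cases. With a constant per-school score and CG values from T2 the model has full rank, and only the T1 term is interpretable, under the substitution assumption described above. In all cases the result is a non-randomised association.

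The rank results assume that no usable CG component score exists for T1, which follows from the survey schedule and the delayed start. They do not depend on effect size or prevalence.

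Severity is moderate. A reader might take this as a threat to the trial's main result, but the third objective is exploratory, and the primary analysis, randomisation, sample size and data collection are untouched.

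**What to change.** In section {20a}, state how the component variable is coded over time and for the CG, and choose one of two analyses:

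1. Fit component × measurement point within IG schools only, adjusted for school type and the school's T0 prevalence, entered so that they act on the change and not only on the level.
2. Use one constant score per school, with CG values from the T2 survey. Restrict inference to the T1 triple term, and state the assumption that the CG's later implementation represents what it would have implemented a year earlier.

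In either case, delete the sentence on identification and describe the result as an exploratory, non-randomised association.

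The cost is analysis wording only, with no new data. The first option uses half of the schools. The second keeps both groups but rests on an assumption that the trial data cannot verify. The claim about components becomes weaker under both.

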In secondary schools, *Bullying&You* operates in three stages:Preparation (2 months): Principals and core team members become familiar with the program.Implementation (12 months): Pupils work through 6 lessons of the basic course (definition and forms of bullying; individual causes and group mechanisms; prevalence and adverse consequences of bullying; different roles in bullying situations; options for intervention; good togetherness in class). Each lesson consists of an eLearning unit, a short survey, a quiz, and a class meeting. Independent from grade, each pupil gets the same 6 lessons to build up a solid base for the further prevention work. Teachers work on the same 6 topics via eLearning containing target-specific and more detailed information (e.g. the influence of school conditions on bullying development; on-the-spot intervention in 7 steps; guidelines for break supervision and class room management). The core team develops and implements school-specific concepts to reduce bullying and to improve school climate.Continuation (from second program year onwards): Pupils work on age-specific topics in advanced courses, consisting of 4 lessons per school year (grade 6: direct and indirect bullying, grade 7: cyberbullying and gender differences, grade 8: role models and legal aspects, grade 9: prosocial behaviour and helping; grade 5 receives the basic course). Each lesson comprises an eLearning unit, a short survey, and a class meeting. Teachers stay on topic through repetition, peer exchange, pedagogical days, and practical lessons. The core team continuously evaluates and optimizes the anti-bullying concepts of their school.

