### Methods in analysis to handle protocol non-adherence and any statistical methods to handle missing data {20c}

The analysis is an intention to treat analysis; whole schools were randomly assigned to the two conditions intervention group vs. control group. In order to enable sub-analyses differentiated by program dose, a score based on the intensity of the central program components will be created for each school.

Sensitivity analyses are done on the complete-case sample, i.e. excluding schools where measurement points are missing.

To deal with our fourth objective (individual characteristics predicting the program success at the individual level), the association of questionnaires from different time points to pupils is required. Therefore, individual codes with a Levenshtein distance not greater than 2 are assigned to the same pupil. Apart from this strategy to reduce missings, no missing data is imputed.

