Despite the well-designed trial and the promising anti-bullying intervention, we may also face some barriers. First, some schools might not be able to profit from the various advantages of the digital program components (e.g. eLearning) because they lack the required digital infrastructure. At times, teachers in Germany are also still rather sceptical or feel insecure when dealing with digital media. These challenges can be addressed by offering modifications of the relevant program components, as well as by providing guidelines for, and intuitive designs of, the digital media. Second, interrelations of aspects affecting the program effectiveness are very complex: some program components might only work for certain age groups, certain forms of bullying, or a particular gender. Further, a program component may not be effective on its own, but in combination with others, proves to be successful. Mediators and moderators of preventive programs have scarcely been researched (‘*What works, for whom, and under what circumstances*’, [47], p. 438). Due to this complexity, we will need to analyse our data carefully to draw our conclusions. Third, implementing a whole-school approach may take some time. Thus, changes in bullying and mental health might not yet be significant after only 1 or 2 years of program implementation. As our evaluation study only comprises 3 measurement points (baseline T0; follow-up + 12 months T1; follow-up + 24 months T2), additional follow-up time points are highly desirable to evaluate the long-term effectiveness and sustainability of *Bullying&You*.

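### Objective three's one-component-at-a-time models describe associations; they do not identify the effect of a specific program component, as the plan says they do

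*Protocol article*

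**What the plan says.** Under Statistical methods for primary and secondary outcomes {20a}, the implementation of one component (from teacher surveys and eLearning use) is added to the primary model as a covariate, with its interactions with group and measurement point. The section concludes: "The triple interaction allows for the identification of the effectiveness of a specific program component. The analysis is repeated for different components". No term for the other components is described. The same section adds: "All calculations are performed with a significance level of 0.05".

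Intervention description {11a} says of the first program year in secondary schools: "Each lesson consists of an eLearning unit, a short survey, a quiz, and a class meeting". Lessons in later years again combine eLearning, a survey and a class meeting. Table 1 makes one core team in each school responsible for organizing the components.

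The Discussion warns that "a program component may not be effective on its own, but in combination with others, proves to be successful". The section on non-adherence and missing data {20c} plans dose sub-analyses, for which "a score based on the intensity of the central program components will be created for each school".

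**The concern.** Allocation was by whole school (Sequence generation {16a}), so how much of each component a school delivers is observational, even inside a randomized trial. At T1 the teacher survey goes to the intervention group only (Plans for assessment and collection of outcomes {18a}). The component contrast at T1 therefore rests on differences between intervention schools or classes that nobody randomized.

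If schools that deliver one component well also tend to deliver the others well, a coefficient for that component alone mixes its own effect with theirs. An inert component can look effective because of the company it keeps. The identification sentence also sits badly with the Discussion's remark that a component may work only in combination. The Introduction hopes that these results will inform policy and later programs, so a wrong attribution could carry over into which components are kept or dropped.

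**Working it through.** **Plan's own figure first.** Inputs from Sample size {14}: "Baseline bullying prevalence is estimated to be 15%, and the intervention is expected to lead to a relative reduction in bullying of 25" percent; "15 secondary schools per group with 10 classes per school and 5 primary schools per group with 4 classes per school"; 25 pupils per class; SD 0.2 between schools and 0.4 between classes on the logit scale. Per group this is 15 × 10 + 5 × 4 = 170 classes and 170 × 25 = 4,250 pupils. The prevalence falls from 0.15 to 0.15 × 0.75 = 0.1125, and logit(0.15) − logit(0.1125) = 0.331.

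Variance of the difference in changes, with the class effect drawn anew at each measurement point:

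3/(4250 × 0.15 × 0.85) + 1/(4250 × 0.1125 × 0.8875) + 4 × 0.16/170 = 0.0079 + 0.0038 = 0.0117, so SE = 0.108.

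Power = Φ(0.331/0.108 − 1.96) = 86.5%, which agrees with "with 40 schools and 8500 pupils (4250 IG and 4250 CG) the power would be 86" percent. (With one class effect shared by both points, power would be 96.1%.) The noise inputs are therefore usable. The 86% concerns the primary comparison; no figure is given for objective three.

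**Noise in one school's change.** For a school of 10 classes, the SD of the change in logit prevalence is

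√{[0.16 + 1/(25 × 0.1275) + 0.16 + 1/(25 × 0.0998)]/10} = √(1.034/10) = 0.32,

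where 0.1275 = 0.15 × 0.85 and 0.0998 = 0.1125 × 0.8875.

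**Assumptions not in the documents.** Ten components, of which one is active and carries the whole program effect. Mean uptake 60%, SD 25 points, so the effect per SD of uptake is 0.331/0.60 × 0.25 = 0.138. All pairs of components share the same correlation r. Change in the 20 intervention schools is regressed on a single component, as a stand-in for the three-level model.

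**Result for one inert component modelled alone, nominal 5%:**

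| r | flagged |
|---|---|
| 0 | 5% |
| 0.3 | 8% |
| 0.5 | 13% |
| 0.7 | 21% |
| 0.9 | 36% |

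Repeat runs differ by about one point. At r = 0.9 the truly active component is flagged in about 42%, so the two are hardly told apart.

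**Second set-up.** One active and one inert component, the plan's real school sizes, binomial data, uptake SD 20 or 30 points, and implementation measured by school or by class. The inert component's coefficient is 0.3, 0.5, 0.7 and 0.9 of the active one's at those correlations, and it is flagged in 9–14%, 13–23% and 20–34% at 0.5, 0.7 and 0.9.

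**What adjustment does.** With both components in the second set-up's model, the inert one is flagged in 4.3–6.2% at every correlation. The price is precision: the active component's SE rises about 1.4-fold at r = 0.7 and 2.2- to 2.4-fold at 0.9. Its power falls from 23–41% to 14–23% and 8–12% respectively.

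Adjusting instead for the mean of the other nine components returns the rate to 5% only when all pairs are equally correlated. If the active and inert components correlate 0.9 and all other pairs 0.3 to 0.5, the inert one is still flagged in 14–21%.

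**The case against.** The strongest reply is that the components do vary separately. Schools without the equipment may drop pupil eLearning or have it led by the teacher ({11b}). The pedagogical day and project day are optional (Table 1). Primary pupils have class meetings but no eLearning ({11a}), and Recruitment {15} raised the primary target to 13 of the 40 schools. Class teachers report eLearning units, class meetings and project days as separate items ({18a}). All of this stands. A reader might infer from the lesson package that eLearning can never be told apart from the class meeting; the documents do not support that.

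A reader might also infer that inert components will be declared effective. That does not follow either: even at r = 0.9 an inert component goes unflagged in 64% of simulated trials, and the correlation is unknown.

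Third, the Objectives call these analyses exploratory, and the Discussion promises careful interpretation. That limits the damage but changes neither the model nor the sentence, which claims identification.

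Finally, further component models could be set out in an analysis plan that is not shown. That is fair for their detail. It does not excuse a stated property that the described model lacks.

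**Conclusion.** The identification sentence is wrong as written. It credits single-component models of non-randomized, probably correlated uptake with a property they do not have. The bias is a share of the neighboring components' effect roughly equal to the correlation. False flags run at about 13%, 21% and 36% for correlations of 0.5, 0.7 and 0.9, and there is no excess at zero correlation. These sizes rest on the assumed correlations, on one component carrying the whole effect, on the assumed uptake distribution, and on regressions of change in place of the mixed model. The direction needs only a positive correlation in uptake and a real effect of a companion component. The consequence is confined to what objective three may conclude.

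**What to change.** 1. Replace the identification sentence by one to this effect: *the triple interaction describes the association of a component's implementation with change in bullying; it does not separate that component from others delivered with it or from general school implementation.*
2. Keep the single-component models. Beside each, report a model that also contains the measured components most closely tied to it (for example class meetings with eLearning in secondary schools), or the planned dose score computed without that component, with the same interactions. Direct adjustment for the close companion is the safer of the two where components are bundled, because the score can leave much of the excess.
3. Report the observed correlations between component measures.
4. State that the adjusted models have low power with 20 intervention schools and do not remove confounding by school motivation. Do not name a component as effective from the unadjusted model alone.

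The cost is a wording change and some extra models on data already planned. Adjustment reaches only components that are measured; the article lists no implementation measure for the quiz or the short survey within a lesson. The real price is imprecision, which is why the adjusted models should stand beside the planned ones and not replace them.
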